## Abstract

**Background:**

Chronic chagasic cardiomyopathy is an inflammatory disease that occurs in approximately 30% of patients infected by the protozoan *Trypanosoma cruzi*, and it has a profile of high morbidity and mortality. The worst prognosis and the progression of this cardiomyopathy are associated with an exacerbated immune response and the production of proinflammatory cytokines, which also occur in other cardiomyopathies. Some nutrients, including omega-3 polyunsaturated fatty acids (PUFAs), promote the inhibition and/or stimulation of cytokine production. The objective of this trial is to study the effects of omega-3 PUFA supplementation on the inflammatory response and lipid profile in patients with chronic chagasic cardiomyopathy.

**Methods/Design:**

This is a parallel, randomized, placebo-controlled, double-blind clinical trial with 40 patients that will be conducted at a reference unit for Chagas disease patients, where the patients will be selected. The study will include patients with chronic chagasic cardiomyopathy who are 18 years of age or older. The exclusion criteria are (a) ongoing diarrheal disease, (b) inflammatory bowel disease, (c) diabetes or other endocrine disease, (d) use of fibrates, niacin, or statins, (e) use of anti-inflammatory drugs, (f) pregnant and lactating women, (g) use of vitamin, mineral, or omega-3 supplementation during the previous 30 days, (h) hospital admission during the study, and (i) other associated cardiomyopathies. The intervention will be treatment with omega-3 PUFAs at a dose of 3 g/day for 8 weeks, compared to placebo (corn oil). The primary endpoints will be the concentrations of inflammatory markers (interleukin (IL)-1, IL-2, IL-4, IL-6, IL-10, tumor necrosis factor (TNF)α, interferon (IFN)γ, and transforming growth factor (TGF)β). Secondary endpoints will be the fasting glucose, lipid, and anthropometric profiles. For statistical analysis, we plan to run either a t test or Wilcoxon test (numerical variables) and Pearson’s χ^2^ or Fisher’s exact test (categorical data), as appropriate.

**Discussion:**

Evidence suggests that the anti-inflammatory action of omega-3 PUFAs may have beneficial effects on chronic chagasic cardiomyopathy, as shown for other cardiomyopathies, due to improved control of the inflammatory response. At the end of the study, we predict that patients will have lower inflammatory markers and an improved metabolic and anthropometric profile.

**Trial registration:**

Current Controlled Trials NCT01863576

## Background

Chagas disease is endemic in Latin American countries, where approximately 8 to 10 million people are infected with *Trypanosoma cruzi*[1]. In Brazil, the number of infected people is approximately 1.9 million, or 1% of the Brazilian population [2].

The etiologic diagnosis of Chagas disease is performed by detection of the parasite by parasitological methods (direct or indirect) and confirmed by two different serological techniques indirect immunofluorescence and enzyme-linked immunosorbent assay (ELISA) [3].

Chagas disease has two distinct clinical phases: acute and chronic [3]. The chronic phase has three forms: indeterminate, cardiac involvement, and/or digestive involvement [3-5]. In most cases, acute disease is not recognized at onset, and the individual remains asymptomatic with no evidence of damage to any organ but with reactive serology for Chagas disease and low parasitemia during the chronic phase [4]. After two or more decades, 20% to 30% of patients progress to the cardiac stage of the disease, when the majority of the deaths and severe complications related to the disease occur [6-8]. Therefore, chronic chagasic cardiomyopathy (CCC) is an important clinical form of Chagas disease due to its impact on morbidity and its high mortality, worsening of the quality of life, and limitation of the ability to work. It is characterized by a myocarditis with multifocal mononuclear inflammatory infiltrates, varying degrees of fibrosis, constant low-grade tissue parasitism, and low or undetectable parasitemia [9] and it occurs earlier and more severely in males [8,10]. Patients in the chronic cardiac phase may manifest heart failure, ventricular and atrial arrhythmias, atrioventricular blocks, thromboembolism, stroke, and sudden death [2,7,11], which together carry a high economic and mortality burden.

Once settled, CCC is progressive and tends worsen due to overlap with inflammation, cell destruction, and fibrosis. Some hypotheses have been proposed to explain the nature of the cardiac inflammatory reaction, mainly persistent heart immune response and reaction to the parasite [12]. Cytokines are important mediators in the maintenance of the inflammatory process, and they can stimulate or inhibit the immune response [13]. Among the several cytokines studied in *T. cruzi* infection, interferon γ (IFNγ) has been associated with host resistance to infection in both experimental models and humans [14,15]. Transforming growth factor β (TGFβ) production is increased in *T. cruzi* infection, and this increase is most likely related to the fibrotic process observed in CCC [16]. These results suggest that cytokines play essential roles in controlling CCC morbidity [17-19].

Some nutrients are associated with the inhibition and/or stimulation of cytokine production, including polyunsaturated fatty acids (PUFAs). Omega-3 PUFAs (linolenic acid, eicosapentaenoic acid, and docosahexaenoic acid) are found in vegetables (soy, canola, linseed) and cold-water fish (mackerel, sardines, salmon, herring). PUFAs are precursors to the biosynthesis of several important metabolites, especially eicosanoids (prostaglandins, leukotrienes, thromboxanes, lipoxins, and others), synthesized from arachidonic acid [20]. Omega-6 PUFAs (such as linoleic acid: 18:2n-6) and omega-3 PUFAs (such as linolenic acid: 18:3n-3) are fundamental to the body and have important roles in cell metabolism, including influencing membrane fluidity, promoting the release of cytokines, and acting as adhesion molecules on macrophages. Thus, changes in their synthesis and metabolism may be associated with endothelial and hemodynamic changes that contribute to the increase in cardiovascular morbidity and mortality [21].

The fatty acid composition of inflammatory cells can be modified by increasing the intake of marine *n*-3 fatty acids, which leads to a higher content of eicosapentaenoic acid (EPA) and docosahexaenoic acid (DHA). A number of cell culture studies have reported that both EPA and DHA decrease the activation of the transcription factor nuclear factor κB (NFκB) in response to inflammatory stimuli, such as lipopolysaccharide and inflammatory cytokines [22]. Omega-3 PUFAs reduce arachidonic acid content in cell membranes, resulting in the synthesis of eicosanoids that have weaker inflammatory properties than the eicosanoids derived from omega-6 PUFAs [23].

Omega-3 supplementation is safe and well tolerated in infectious disease as demonstrated in HIV-infected patients treated with antiretroviral therapy [24,25], and on host resistance to infection from *Plasmodium berghei* or *Plasmodium falciparum*, the causative agents of malaria [26], which like Chagas disease is a parasitic infection.

Several studies involving supplementation of the diet with marine *n*-3 PUFAs in healthy human volunteers have demonstrated decreased production of tumor necrosis factor α (TNFα), interleukin 1β (IL-1β), IL-2, and IL-6 [22,23,27]. Omega-3 PUFA supplementation for 8 weeks has been associated with an increase of peripheral mononuclear cells with high concentrations of EPA and DHA, which have an immunomodulating effect [28]. In healthy adults, fish oil supplementation at 5 mL/day for 8 weeks reduced the production of IL-6 but did not change the production of IL-10, TNFα, or IFNγ [29]. Long-chain omega-3 PUFA (EPA and DHA) plasma levels are inversely associated with the risk of sudden death [30] and may reduce the risk of ischemic heart disease [31]. EPA and DHA are also involved in the reduction of plasma very-low-density lipoprotein cholesterol (VLDL-c) and triglycerides [32].

A study conducted by the Italian group GISSI-HF at 326 cardiology sites and 31 internal medicine sites selected 6,975 patients with heart failure diagnosis to receive 1 daily capsule containing 1 g of omega-3 PUFAs (n = 3,494) or placebo (n = 3,481) [33]. The total mortality of the supplemented group was 27%, and that of the placebo group was 29% (adjusted HR 0.91; 95.5% confidence interval (CI) 0.833 to 0.998; *P* = 0.041). Hospital admissions due to cardiovascular events were 57% in the omega-3 PUFA group versus 59% in the placebo group (adjusted HR 0.92; 99% CI 0.849 to 0.999; *P* = 0.009). The advantages of *n*-3 PUFAs, which were reduced fatal events and hospital admissions from cardiovascular causes, suggest that they have an effect on the mechanisms leading to progression of heart failure [33].

Supplementation with 1 g/day of omega-3 PUFAs in capsules can decrease cardiovascular events by 10% (death, myocardial infarction, stroke) in coronary arterial disease patients [34]. Some studies that assessed the effect of omega-3 supplementation on the immune response used EPA and/or DHA at 1 g to 9 g per day, similar to the ingestion levels of Greenland Eskimos: 6 to 14 g/day, corresponding to 2.7% to 6.3% of their total calorie intake. The highest doses can reduce arachidonic acid in peripheral mononuclear cells [35].

Studies conducted in heart failure patients have not shown adverse events after omega-3 supplementation [33,36]. In contrast, studies in pregnant women and cancer patients have reported gastrointestinal changes (diarrhea, flatulence, gastroesophageal reflux, nausea), although no differences between the treatment and placebo groups were noted [37,38].

Few studies have evaluated the nutritional status of Chagas patients. Three studies have evaluated patients with the digestive form of the disease. In two of these studies [39,40], there was a high prevalence of malnutrition (>60%). The other study evaluated ten patients diagnosed as having megaesophagus, and only one had malnutrition. The others were eutrophic or overweight [41]. A study performed in São Paulo, Brazil, assessed the nutritional state of 66 Chagas patients and found a high prevalence of overweight and obesity (94%) and large waist circumference (55%). The indeterminate form of the disease was the most prevalent and constituted 71% of cases [42]. There are no reports in the literature on the nutritional assessment of CCC patients.

Supplementation with omega-3 PUFAs may lead to increased bodyweight in patients with heart cachexia, as reported by a study that assessed 14 patients with severe heart failure supplemented with 8 g/day omega-3 PUFAs or placebo [43].

Although several studies have shown the beneficial effects of polyunsaturated fatty acids on inflammatory processes, dyslipidemia, and cardiovascular diseases, there are no reports about food intake and PUFA supplementation in CCC patients. Thus, the objective of this study is to assess the effects of omega-3 PUFA supplementation on the lipid profile and the proinflammatory and anti-inflammatory cytokine profiles in CCC patients.

## Methods/Design

### Study design

This is a parallel, double-blind, placebo-controlled clinical trial with balanced randomization (1:1).

### Settings

The proposed clinical trial will be held at a single site, the Evandro Chagas Clinical Research Institute (IPEC), which is one of the technical scientific units of the Oswaldo Cruz Foundation (Fiocruz). IPEC is a 93-year-old institution that is fully dedicated to clinical research on infectious diseases, including Chagas disease. IPEC is a major reference center for Chagas disease research, care, and training.

### Participants (inclusion and exclusion criteria)

Patients will be recruited from the cardiology ambulatory service at IPEC/Fiocruz, Rio de Janeiro, Brazil, during the period determined for screening until the minimum estimated sample size is reached. All patients had a previous epidemiologic history of Chagas disease confirmed with at least two Chagas serology tests (indirect immunofluorescence and ELISA), and clinical evaluations, electrocardiographic and echocardiographic data obtained recently. Selected patients will be older than 18 years, males and females with CCC at stage B (no heart failure symptoms but with segmental or global left ventricular systolic dysfunction by echocardiogram), stage C (symptomatic heart failure), or stage D (end-stage heart failure), according to the current Brazilian Chagas disease consensus [3]. The following exclusion criteria will be applied: diarrheal disease; inflammatory bowel syndrome; diagnosis of diabetes or other endocrine pathologies; use of fibrates, niacin, or statins; use of anti-inflammatory drugs; pregnant and lactating women; vitamin mineral or omega-3 supplementation during the previous 30 days; hospital admission during the study; and the presence of cardiomyopathies other than CCC.

### Interventions: omega-3 versus corn oil placebo

Each participant will receive five omega-3 capsules per day (1.8 g EPA and 1.2 g DHA) or placebo for 8 weeks (Figure 1). The omega-3 and corn oil capsules will be provided by Relthy Laboratórios Ltda. (Brazilian Health Surveillance Agency (Agência Nacional de Vigilância Sanitária (ANVISA)) registration: 6.2582.0022.001-1).

**Figure 1 F1:**
[figure not shown]
Study flow diagram for omega-3 supplementation in patients with chronic chagasic cardiomyopathy.

### Endpoints

The primary endpoint of this study will be the cytokine profile. IL-1, IL-2, IL-4, IL-6, IL-10, TNFα, IFNγ, and TGFβ will be measured in the serum of patients using specific sandwich enzyme-linked immunosorbent assays. Capture and detection antibodies will be obtained from eBioscience (San Diego, CA, USA). The tests will be conducted according to the manufacturer’s instructions and performed in triplicate.

The first secondary endpoint will be the lipid profile. Total cholesterol, triglycerides, and high-density lipoprotein cholesterol (HDL-c) will be measured with enzymatic colorimetric assays using Siemens reagents on a Siemens Dimension RXL chemistry analyzer (Siemens Healthcare Diagnostics, Tarrytown, NY, USA). Low-density lipoprotein cholesterol (LDL-c) and VLDL-c will be calculated according to the Friedewald equation [44].

Another secondary endpoint of this trial will be anthropometric measures. The anthropometric assessment will consist of body mass index (BMI), waist circumference, tricipital skinfold thickness, and arm circumference [45,46]. BMI will be determined using the standard formula: BMI = weight/height^2^[47].

### Procedures, follow-up, and data collection

After patients are selected by cardiologists, they will be seen by study nutritionists, who will explain the study procedures to the patients and administer the free and informed consent form. The patients who agree to participate in the study will sign the consent form and undergo the initial assessment.

The following data will be collected and evaluated in the study: sociodemographic data (age, sex, ethnicity/race, education, and domicile), clinical data (functional class and vital signs), alcoholism, smoking, prescription drugs, 3-day food record [48], 24-h recall [49], anthropometric assessment (height, weight, BMI, waist circumference, tricipital skinfold thickness, and arm circumference), lipid profile (total cholesterol, triglycerides, HDL-c, LDL-c, and VLDL-c), and cytokines (IL-1, IL-2, IL-4, IL-6, IL-10, TNFα, IFNγ, and TGFβ). Clinical, nutritional, and anthropometric assessments will take place immediately before starting the intervention and after 4 and 8 weeks during the study; lipid profile and cytokines will be evaluated before the intervention and at the end of 8 weeks. Each patient will be followed for 8 weeks.

Compliance with study treatment will be assessed by the 3-day treatment recall and the number of omega-3/placebo capsules returned. At every visit, the patients will be asked about the number of doses of the prescribed treatment that they did not take during the previous 3 days, and the ratio between the number of doses taken and the number prescribed will be calculated. The capsules will be dispensed at the beginning of the study and after 4 weeks, and the returned capsules will be verified at weeks 4 and 8.

The dietary omega-3 PUFA intake will be followed-up during the study (first visit and weeks 4 and 8) by analyzing the 24-h recall and 3-day food record, which are considered indirect methods of analyzing the diet, current dietary standards of a certain population, and their development over time [50].

Patients may be excluded from the study in case of complications during follow-up, such as significant changes in intestinal transit, use of anti-inflammatory drugs, and hospital admissions. Other complications will be assessed by the study team. All endpoints will be collected at time 0 and 8 weeks after omega-3/placebo supplementation starts.

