### Safety monitoring

Patients will be followed up by a multidisciplinary team at three time points: study start, week 4, and week 8. Possible complications will be assessed by the study cardiologist and pharmacist. The safety assessment will consist of monitoring adverse events, such as changes in the digestive tract, physical exams, and laboratory tests. Events, onset, and duration will be reported to the cardiologist, who will determine if it is necessary to suspend supplement use. Regular intake of omega-3 PUFAs is not a risk to health. According to the US Food and Drug Administration (FDA), the maximum intake of 3 g/day EPA + DHA is considered safe [51].

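### Randomised patients may be excluded for events after treatment starts, leaving them without a week-8 cytokine value; the comparison can be biased if exclusions differ by arm

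*Protocol article*

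**What the plan says.** Four places in the protocol article bear on this.

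- *Procedures, follow-up, and data collection*: "Patients may be excluded from the study in case of complications during follow-up, such as significant changes in intestinal transit", followed by "use of anti-inflammatory drugs, and hospital admissions". The next sentence leaves the list open: "Other complications will be assessed by the study team". The same section schedules lipids and cytokines at baseline and week 8 only, says each patient is followed for 8 weeks, and says all endpoints are collected at both times.
- *Participants (inclusion and exclusion criteria)*, and the Abstract: the exclusion list includes "hospital admission during the study". Patients in stages B, C and D are eligible, up to "stage D (end-stage heart failure").
- *Safety monitoring*: safety assessment includes "monitoring adverse events, such as changes in the digestive tract". Whether to suspend the supplement is a separate decision for the cardiologist.
- *Randomization and concealment*: allocation takes place after screening and after all baseline assessments are complete.

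**The concern.** A criterion that can be met only after allocation is not an eligibility criterion. It selects among patients who have already been randomised. The named triggers are unlikely to be a random draw. Bowel change is an adverse event that the trial itself monitors. Anti-inflammatory use and admission plausibly go with inflammation, which is the outcome. The trial also enrols patients with symptomatic and end-stage heart failure.

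Two things are at stake. First, if those removed have higher or lower cytokines than those who stay, and removal differs between arms, the week-8 contrast no longer estimates the effect of assignment. Second, the loss cannot be repaired. With no cytokine sample between baseline and week 8, an analysis plan written later cannot recover a week-8 sample that was never drawn. That is why the point belongs to the protocol and is not a detail to leave to the SAP.

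**Working it through.** **1. Is the rule really post-randomisation, and is it more than stopping treatment?** The follow-up section speaks of complications during follow-up, so it applies after allocation. The admission criterion in the eligibility section refers to admission while the study is running, so it cannot be checked at screening. *Safety monitoring* already covers suspension of the supplement as its own decision. Exclusion from the study is therefore a further step.

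**2. What is lost per excluded patient?** Cytokine times are week 0 and week 8. A patient who leaves before week 8 contributes a baseline value only.

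**3. The plan's sample size and the room it leaves.** *Minimum sample size estimation* gives IFNγ 3,986 ± 738 and 2,922 ± 1,275 pg/mL, power 0.8 and α 5%. I treat these as two independent groups with a two-sided test, which the article does not state.

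- Difference: 3,986 − 2,922 = 1,064.
- n per arm = (738² + 1,275²)(1.960 + 0.842)² / 1,064² = 15.05, so 16 per arm, 32 in total.
- The stated 40 is not reproduced from these inputs, but it exceeds what they need. (32/0.8 = 40 would fit an allowance for 20% loss; none is stated.)
- Power with unequal variances (Welch): 0.88 at 20 per arm, 0.79 at 16, 0.73 at 14. The normal approximation gives 0.90, 0.82 and 0.77.

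Lost power is therefore a secondary matter.

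**4. Bias under an assumed imbalance.** The documents give no exclusion rates, so everything in this step is illustration. Assume 20 per arm, no true effect, a week-8 cytokine with SD 1, and an exclusion propensity with correlation ρ to that cytokine. The k patients with the highest propensity in an arm are excluded. The expected mean of those who stay is

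−ρ × (sum of the k largest expected normal order statistics out of 20) / (20 − k).

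- The five largest order statistics are 1.867, 1.408, 1.131, 0.921 and 0.745.
- k = 5 (omega-3): 6.072/15 = 0.405.
- k = 2 (placebo): 3.275/18 = 0.182.
- Bias = ρ × (0.405 − 0.182) = 0.223ρ, in favour of omega-3.

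| ρ | Bias (SD) | Type I error, 5 v 2 (simulated) |
|---|---|---|
| 0.3 | 0.07 | about 5.6% |
| 0.5 | 0.11 | about 7% |
| 0.8 | 0.18 | about 11% |

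The average-variance SD is √((738² + 1,275²)/2) = 1,041.7 pg/mL, so 0.18 SD is about 190 pg/mL against the planned difference of 1,064.

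**5. What drives those figures?**

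- Equal exclusion, 5 v 5: no bias, yet type I error is about 6% at ρ = 0.5 and 7 to 8% at ρ = 0.8. Removing exactly the top-ranked patients trims the sample and shrinks its SD. Part of the inflation in the table comes from that, not from imbalance.
- Milder imbalance, 3 v 2 at ρ = 0.5: bias 0.04 SD, type I error 5.7%.
- Reversed imbalance, 2 v 5: the same bias, against omega-3.
- Exclusion by probability, not by fixed count (20,000 runs, ρ from 0.3 to 0.6): 10% v 10%, no bias and about 5% type I error; 20% v 10%, 0.05 to 0.09 SD and 5.1 to 5.8%; 30% v 10%, 0.09 to 0.18 SD and 5.4 to 8.1%; 30% v 5%, 0.12 to 0.23 SD and 6.0 to 9.8%.

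**The case against.** The case on the other side has real force.

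- **The wording is discretionary and concerns the study, not the analysis.** A reader might infer that the plan sets out to compare event-free completers. The article does not say so. *Statistical methods* compares the two groups and defines no completer set, and the follow-up section says each patient is followed for 8 weeks and all endpoints are collected. The analysis population may be defined in a document not shown. This stands, and it makes the point conditional. It does not remove it: nothing says that an excluded patient still gives a week-8 sample, and discretion without criteria does not make selection safer.
- **The article's own evidence does not point to a large imbalance.** The Background mentions gastrointestinal changes in supplementation studies of pregnant women and cancer patients, but adds that the arms did not differ. It reports no adverse events after supplementation in heart failure studies. In the large heart failure trial, cardiovascular admissions were 57% on omega-3 and 59% on placebo, which if anything suggests more placebo exclusions. This stands, so neither size nor direction of bias can be claimed as known. Yet the article presents that admissions result (HR 0.92) as a benefit of the supplement, so it treats one trigger as responsive to treatment.
- **Blinding limits selective removal.** The nutritionists and physician are blinded. That protects against biased judgement, not against true differences in event rates. *Safety monitoring* also names a pharmacist among those who assess complications, and the dispensing pharmacist can see the lot codes. If they are the same person, the protection is incomplete.
- **Safety follow-up.** A reader might infer that adverse-event follow-up ends on exclusion. The article does not say this; events, onset and duration are to be reported to the cardiologist.

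**Conclusion.** The point holds as a conditional one. The protocol permits removal of randomised patients for events that the supplement, the disease or inflammation can influence, and it lists a post-enrolment event as an exclusion criterion. With cytokines taken only at weeks 0 and 8, each early exclusion costs the primary outcome for good. If exclusions differ by arm and relate to cytokine level, the comparison is biased: about 0.07 to 0.18 SD for 5 v 2 exclusions and correlations of 0.3 to 0.8, and up to 0.23 SD in the other scenarios tried. Those rates and correlations are assumptions. Exclusion at the same rate and for the same reasons in both arms, with no true effect, gives no bias. A reader might infer that the trial is biased as planned, that type I error is 11%, or that it is underpowered; the documents support none of these. The defect is in the rule, and it is worth correcting promptly because *Trial status* says recruitment is under way.

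**What to change.** Reconcile the Abstract, the eligibility section, the follow-up section and *Safety monitoring* so that:

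1. Eligibility criteria apply only before randomisation. "hospital admission during the study" comes off that list and is recorded as a follow-up event.
2. Stopping the supplement is kept separate from leaving the study. When the supplement is stopped is a clinical decision, on which this point takes no position.
3. The planned week-8 sample is drawn from every randomised patient who still consents, whether or not capsules are still being taken.
4. All patients are analysed in their assigned arm.
5. Bowel changes, anti-inflammatory use, admissions and other complications are reported by arm.
6. The event-free set is kept as a labelled sensitivity analysis.

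The cost is a wording amendment and week-8 draws that are already scheduled. There is one small downside: values taken during acute illness or anti-inflammatory use add noise and may dilute a mechanistic effect. The sensitivity analysis addresses that.
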